**INTRODUCTION**

Asthma and COPD are two respiratory conditions characterized by chronic inflammation of the lungs resulting in respiratory impairment and distress (1, 2). They are considered a serious global problem affecting millions of people all over the world (3, 4).

The delivery of drugs by inhalation is an integral component for the treatment and management of respiratory conditions. Inhaled medicines are rapidly directed to the airways, allowing for rapid onset which permits the administration of lower doses, limiting potential side effects (5).

Inhaled corticosteroids (ICS) and bronchodilators, given on a regular basis, are considered central to symptoms management in asthma and COPD respectively and decrease in their exacerbation rates (1, 2).

The correct use of inhalers requires special techniques that are crucial for the optimal drug delivery and deposition in its site of action and considered mandatory to control respiratory symptoms (6-8). Data shows however, that inhaler mishandling remains a common problem in real life (6). Worldwide up to 80% of people with asthma are unable to use their inhaler device correctly and more than two thirds of patients with COPD make at least one error in using their inhalation device (1, 2).In Jordan, only 35% of asthmatic patients demonstrated correct technique while no data is available for COPD patients (9).

Inhaler misuse has been associated with poor symptom control and disease instability, increased risk of emergency visits and hospitalizations, use of oral corticosteroids, lower quality of life (QoL) and greater health-economic burden (5-7). Educating patients on how to use their inhaler correctly is thus considered crucial for the mastery of good inhaler technique and effective self-management of asthma and COPD (1, 2, 6).

The British thoracic society highlights the necessity of proper inhaler technique: “prescribe inhalers only after patients have received training in the use of the device and have demonstrated satisfactory technique” (10, 11).The Global Initiative for Asthma (GINA) and Global Initiative for Chronic Obstructive Lung Disease (GOLD) also stress to assess and correct poor inhalation technique before stepping up asthma or COPD treatment in patients with uncontrolled condition (1, 2).

The Teach-To-Goal (TTG) approach is considered an effective method to educate patients on the proper use of medications, including inhalers. It consists in in-person oral instructions using an inhaler device with cycles of demonstration and assessment (12, 13). However, after the initial education provided upon inhaler prescription, only few patients later receive information or advice on how to use their inhaler. Inhaler technique deteriorates over time; the improved inhaler technique initially obtained after TTG education wanes within 30 days post-discharge (13, 14).

On these bases, patient education needs to be reinforced. Patients necessitate an effective, portable education that remains easily accessible to them whenever they need it.

Few previous studies have shown technology-based interventions to be effective at improving self-management of few chronic conditions, including asthma however, none of these studies has been conducted in Jordan (15-19).

The present project thus aims to provide asthma and COPD patients in Jordan with a novel inhaler education approach, through the development of a Teach-To-Goal video-based education in Arabic that would be easily accessible post-discharge from patients’ home. The impact of this novel approach on inhaler technique as well as other clinical parameters such as asthma/COPD control, adherence to inhaler, and quality of life will also be assessed.

**Objectives:**

The objectives of the present research proposal are:

- To assess inhaler techniques, level of asthma/COPD control, medication adherence, quality of life and asthma- and COPD-related knowledge among Jordanian patients with asthma or COPD.
- To evaluate and compare the effectiveness of two methods of patient education on mastering inhaler technique among Jordanian patients with asthma and COPD; the traditional in-person TTG education and the video-based TTG one. This will be done immediately after the intervention and three months later.
- Assess the impact of the two interventions at the level of asthma and COPD control, medication adherence and quality of life on Jordanian patients with asthma and COPD after 3 months of the intervention.
- To evaluate the impact of the video-based TTG patient education on asthmatic and COPD patients with low literacy in comparison to high literacy patients.

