**METHODOLOGY**

**Study design and participants:**

A prospective, open label, randomized controlled trial will be conducted at the Jordan University Hospital (JUH) in cooperation with [name] [name] from the respiratory team at (JUH), the Jordan Hospital and others public hospitals. An ethical approval will be obtained from the institutional review boards of the JUH, the Jordan Hospital and the Ministry of Health before starting the study.

All eligible patients between 17 and 80 years old attending the respiratory outpatient or the inpatient respiratory clinic in the hospitals will be invited to join the study and asked to sign a consent form before their participation.

Inclusion criteria include patients with an established asthma or COPD diagnosis by a respiratory physician, who were started on inhaler/s (pressurized metered dose inhaler (pMDI), turbohaler, accuhaler, handihaler, and soft mist inhaler) for a minimum of one month and are expected (as prescribed) to continue using their inhalers for a minimum of three months. Immunocompromised patients, patients who have difficulty in communication due to special needs or very severe clinical presentation will be excluded from the study.

Participants will be randomized into two groups. Simple randomization will be adopted; odd number for the educational intervention and even number for control.

Later each group will be provided, by a clinical pharmacist, with a different inhaler technique educational intervention (Non-invasive). The control group patients will receive an in-person TTG education consisting of a brief counseling on the proper use of inhalers followed by assessment. This cycle of assessment and counseling will be repeated up to three times if necessary, until the patient demonstrated correct technique on all steps.

Patients in the intervention group will receive a video-based teach-to-goal intervention on the proper inhaler technique using videos provided by the originator company of each inhaler type. Patients will be asked to watch a video (3-5 minutes in length) followed by assessment. If the assessment reveals incorrect use of the inhaler, the participants will be prompted to watch the video again and repeat until mastery will be demonstrated. If needed, the correct answer will be provided following 3 incorrect attempts. Patients in this group will be provided the video as a multimedia file to access it whenever they need re-education regarding their inhaler technique.

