**Baseline assessment and outcomes:**

At baseline, data regarding demographics, asthma/COPD history, medication use including adverse effects, hospital admissions, and previous systemic corticosteroid use.

Inhaler technique as well as the level of asthma/COPD control, adherence to medication and the patients’ quality of life will be assessed at baseline.

Initially, all participants will be asked to use their inhaler in front of the clinical pharmacist and the proper technique will be assessed by the aid of standardized device-specific inhaler technique checklists (AstraZeneca Pharmaceuticals, GlaxoSmithKline, Boehringer Ingelheim Pharmaceuticals) translated into Arabic. Each checklist includes 9-10 steps, eight of them considered essential for the medication to reach the site of action. A score of 8/10 will be thus considered and classified as correct inhaler technique for all of them.

All participants will be assessed for their level of asthma or COPD control through validated Arabic version of the Asthma Control Test )ACT( or COPD assessment test (CAT) before intervention (38, 39).

Medication adherence and quality of life will be assessed by the Arabic versions of the validated 8-items Morisky medication adherence scale (MMAS) of the St. George’s respiratory questionnaire respectively before and after intervention (2, 40-42).

The primary outcome for this research project is to improve inhaler technique in patients with asthma and COPD. Secondary outcomes include increase the level of asthma and COPD control, improve medication adherence, and quality of life.

After collection of all information and assessment of parameters at baseline, patients will receive either the in-person education or the video-based teach-to-goal intervention. Participants will be then asked to use their inhaler as prescribed by the physician.

All patients will be followed up for 3 months, after which inhaler technique, level of asthma/ COPD control, adherence to medication and the patients’ quality of life will be assessed.

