**Analysis**

All data will be coded and entered to statistical software SPSS (version 23). Continuous variables will be presented as mean ± standard deviation while categorical variables will be presented as counts and percentages. The difference in the responses between the two groups will be examined using unpaired test t-test or Mann-Whitney U test for continuous variables and Chi-square (X2) test or Fisher’s exact test for categorical variables. The impact of the education on the inhaler technique, disease control, quality of life, and adherence within each group over time were examined using McNemar Test for categorical variables and Wilcoxon test for continuous/ordinal variables. All tests will be two-sided and statistical significance will be set at *p*-value ≤ 0.05. Intention to treat analysis will be adopted to handle missing data.

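### Objective 4 needs each patient's literacy, but the protocol names no literacy measure or cut, and as worded it compares literacy levels under the video instead of teaching methods within literacy levels

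*Protocol*

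**What the plan says.** The fourth item under Objectives in the protocol is "To evaluate the impact of the video-based TTG patient education on asthmatic and COPD patients with low literacy in comparison to high literacy patients". It names the video method only. The second and third objectives each name or refer to both teaching methods.

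Under Baseline assessment and outcomes, the data list reads "At baseline, data regarding demographics, asthma/COPD history, medication use including adverse effects, hospital admissions, and previous systemic corticosteroid use". The measured quantities follow: "Inhaler technique as well as the level of asthma/COPD control, adherence to medication and the patients’ quality of life will be assessed at baseline". The section gives a tool for each of these: device checklists for technique, ACT or CAT for control, the 8-item Morisky scale for adherence, and the St. George's questionnaire for quality of life. Literacy does not appear. The secondary outcomes do not mention it either: "Secondary outcomes include increase the level of asthma and COPD control, improve medication adherence, and quality of life".

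Allocation takes no account of literacy: "Simple randomization will be adopted; odd number for the educational intervention and even number for control". The between-arm comparison in the Analysis section is a plain two-group one: "The difference in the responses between the two groups will be examined using unpaired test t-test or Mann-Whitney U test for continuous variables", with chi-square or Fisher's exact test for categorical variables.

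Apart from this objective, literacy appears only in the Literature Review. There the Teach-To-Goal (TTG) method is said to outperform standard education particularly in patients with low health literacy.

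**The concern.** There are two linked problems.

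**The variable is not specified.** The objective needs every patient classified as low or high literacy. A statistical analysis plan can define how to analyse collected data, but it cannot create a baseline variable that nobody recorded. If sites follow the protocol as written, the objective is either left unanswered or rests on an education item that the protocol does not mention and for which it sets no cut. It is also unclear whether general literacy or health literacy is meant.

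**The contrast as worded does not isolate the video.** Patients are randomised to a teaching method, not to a literacy level. A low/high gap among video patients may reflect age, device, baseline technique, or a disadvantage that low-literacy patients have under any teaching. Both arms receive TTG, and the protocol's own background links TTG's benefit to low health literacy. A literacy pattern in the video arm could therefore belong to TTG in general. Only the in-person arm can show whether it belongs to the video.

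At stake is a stated objective that may go unanswered, or that may credit or blame the video for something it did not cause.

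**Working it through.** **1. Objective against data collection.**

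| Needed for objective 4 | Provided in the protocol |
|---|---|
| Literacy measure | None named; demographics are not itemised |
| Definition of low and high | None |
| Comparator | Literal wording: high-literacy patients under the video; the in-person arm is not mentioned |
| Outcome | Not named in the objective |

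**2. What each contrast estimates.** Let the correct-technique rates in high-literacy patients be *h*v (video) and *h*c (in person). Suppose, purely as an illustration, that low-literacy patients do 20 points worse under both methods.

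- Video patients only, high minus low: *h*v − (*h*v − 20) = 20 points.
- Video minus in person, high literacy: *h*v − *h*c.
- Video minus in person, low literacy: (*h*v − 20) − (*h*c − 20) = *h*v − *h*c.
- Arm-by-literacy interaction: 0.

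The literal contrast shows 20 points although the video works equally well in both groups. The 20 is an assumption; the protocol gives no rate by literacy.

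**3. The plan's own sample size.** Inputs from the sample-size paragraph: control rate 40%, an 80% increase, 95% power, 5% significance, 20% dropout. The Analysis section makes tests two-sided. Read as a relative increase, 40% becomes 0.40 × 1.8 = 72%.

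- n = (1.960 + 1.645)² × (0.40×0.60 + 0.72×0.28) / 0.32² = 12.996 × 0.4416 / 0.1024 = 56.05, rounded up to 57 evaluable per arm.
- 57 / (1 − 0.20) = 71.25, rounded up to 72, as stated.

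The figure reproduces, and it is sized for the two-arm comparison only.

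**4. What those numbers allow for the interaction.** Assumptions: 57 evaluable per arm, variance p(1 − p) = 0.24 in every cell, two-sided 5% test, 80% power (multiplier 1.96 + 0.84 = 2.80).

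- Even literacy split, 28.5 per cell: SE = √(4 × 0.24 / 28.5) = 0.184. Detectable interaction: 2.80 × 0.184 = 0.51. Half-width of the 95% CI: 1.96 × 0.184 = 0.36.
- 30% low literacy, cells of 17.1 and 39.9: SE = √(2×0.24/17.1 + 2×0.24/39.9) = 0.200. Detectable interaction: 0.56. Half-width: 0.39.

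**5. Power at smaller interactions.** Assumptions: 58 evaluable per arm (72 × 0.80 = 57.6), in-person rate 40% in both literacy groups, video rate 72% in high-literacy patients, low-literacy share between 20% and 50%.

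| Video rate, low literacy | Interaction | Power |
|---|---|---|
| 60% | 12 points | 8–10% |
| 52% | 20 points | 14–20% |
| 40% (no video benefit) | 32 points | 29–43% |

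Even if the whole planned benefit vanished in low-literacy patients, the trial would more likely than not miss it.

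**6. When to measure.** With 20% dropout, 144 × 0.20 = 28.8, so about 29 of 144 patients would have no literacy value if it were taken only at the 3-month visit.

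**The case against.** **The objective is still answerable.** A reader might infer from the missing instrument that objective 4 cannot be answered at all. The document does not support that. Education level is a common demographic item and a usable proxy. What stands is that the protocol does not say education is recorded, does not equate it with literacy, and gives no cut.

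**Literacy is not lost after follow-up.** A reader might also infer that three months of teaching would make literacy impossible to recover later. Teaching is one encounter with repeated cycles, after which video patients keep the file. Nothing suggests that inhaler training changes general literacy. The real loss is the dropouts.

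**The video-only contrast is one reading.** The sentence does not restrict the analysis to video patients. In a two-arm trial it can also mean asking whether the video effect differs by literacy. That is fair, but the literal wording names only the video, while objectives 2 and 3 cover both methods. A low/high comparison among video patients is also a legitimate description; it misleads only when read as an effect of the video.

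**Change from baseline may remove the gap.** Technique is measured at baseline and the plan examines change within groups. If the literacy gap is present at baseline and both groups gain equally, change largely removes it. If low-literacy patients gain less under both methods, the misattribution remains.

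**Subgroup methods belong in an analysis plan.** Agreed. The missing interaction test in the Analysis section is not the fault here. The faults are the unspecified baseline variable and the wording of the objective.

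**Conclusion.** The point holds in a limited form. Objective 4 depends on a variable for which the protocol names no measure and no cut. Its literal contrast is non-randomised and cannot attribute a literacy gap to the video. This is a gap in specification and an ambiguous comparison; it does not show that the objective is beyond rescue. The primary comparison is unaffected, and 72 per group reproduces under the relative-increase reading.

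The textual finding needs no assumed figure. The size of the limitation does. An interaction of about 51 points (even split) or 56 points (30% low literacy) is needed for 80% power, given a cell variance of 0.24 and 57 evaluable patients per arm. The protocol gives no literacy distribution, so these figures indicate scale only, and the 20-point example is an illustration. The restated comparison would therefore be exploratory. Because literacy itself is not randomised, even a clear interaction could partly reflect age or other factors that go with it.

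The first objective also refers to "quality of life and asthma- and COPD-related knowledge among Jordanian patients", and no knowledge instrument is named. That is a separate, minor gap and does not bear on this conclusion.

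**What to change.** 1. Add a brief literacy measure to the baseline form, or at minimum education level, and state whether general or health literacy is meant. Fix the low/high cut in advance. Record it before allocation, so that it cannot be influenced by the assigned method and is available for patients who later drop out.
2. Restate objective 4 along these lines: to estimate the difference between video-based and in-person TTG in the proportion with correct inhaler technique at 3 months, separately in low- and high-literacy patients, with the arm-by-literacy interaction and its 95% CI. Label it exploratory, because the trial was sized only for the main comparison.
3. If the low/high comparison among video patients is kept, call it descriptive and show the same comparison for the in-person arm beside it.
4. Separately, name a knowledge questionnaire or remove knowledge from objective 1.

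The cost is a few minutes at an interview already planned, some rewording, and accepting that objective 4 will give wide intervals and no firm conclusion. No change in sample size or allocation is required.

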**LITERATURE REVIEW**

Asthma and COPD, two chronic inflammatory conditions of the lungs, affect millions of people all over the world (WHO). Their prevalence is increasing in Jordan and COPD is still largely underdiagnosed and undertreated (20, 21).

Medications delivered through inhaler devices are the mainstay therapy for respiratory conditions (5).Inhaler devices require proper technique crucial for the optimal drug delivery and deposition in its site of action for both controller and reliever (rescue) medications (22). This however needs multiple, complex steps, some of which considered critical to the efficacy of the inhaled treatment, making inhaler devices difficult to use (5, 13).

Incorrect inhaler technique has been reported worldwide in asthma and COPD patients for pressurized metered dose inhalers and dry powder inhalers, with most of these patients being even not aware of having problems is using their device (1, 2, 23).In a recent study conducted in Jordan, only 35% of asthmatic patients demonstrated proper technique, while no studies investigated inhaler misuse in patients with COPD (9).

Poor technique has been associated with increased frequency of inhaler use and frequency of emergency department visits indicating a poorly controlled condition. It has also been associated with higher local and/or systemic side-effects, higher risk of exacerbation, increased use of oral corticosteroid and decreased quality of life in patients with asthma and COPD (22). In Jordan, a cross-sectional study showed that only one-third of asthmatic patients has controlled asthma while no data is available for COPD patients (24).

The GINA, GOLD and the British guidelines strongly address the importance of patient education on inhaler technique, considered crucial for the mastery of good inhaler technique and effective self-management of asthma and COPD (1, 2, 6, 10, 11). Despite its importance, suboptimal education has been reported (6).

Several are the studies that investigated the effect of patient education on the proper use of inhalers and disease control in asthma and COPD (25, 26).In particular, the Teach-To-Goal (TTG) intervention has been demonstrated to be more effective than the standard education usually provided to the patients at hospitals (single brief set of verbal step-by-step instructions) in improving inhaler technique, particularly for those with low health literacy (12, 13, 19, 25, 27).

Teach‐to‐goal (TTG) education is a multi-session patient education used to teach patients self-care skills until they reach behavioural goals (12, 28). It is based on testing effect and allowing memory to be enhanced through the act of retrieving information while learning. It employs initial assessment, instruction, and reassessment with repeated rounds of instruction until mastery is confirmed (12).

Patient education also revealed a better health status in those receiving the intervention reported as higher level of asthma/COPD control, less emergency visits, and lower risk of exacerbations (29-31).

Similarly, in Jordan an inhaler technique training delivered by pharmacist through “show-and-tell” approach enhanced inhaler technique and asthma control in hospitalized asthmatic patients (9).Similar results were also observed in patients with asthma in rural areas in Jordan (14). Two different novel approaches of education using inhaler reminder labels and pharmaceutical pictogram, were also recently investigated in Jordan, demonstrating better inhaler technique in patient with asthma (32, 33).The reminder labels, but not pharmaceutical pictograms also improved asthma control (32, 34). No previous studies have however assessed the relationship between patient education and proper inhaler technique is COPD patients in Jordan.

The positive impact of patient education is not limited to the acquisition of proper device technique but it was also showed to improve adherence to medications in asthma and COPD as well as the patients’ quality of life. In fact, correct use of inhalers is considered an important component in adherence and significantly correlated with a higher health-related quality of life score (6, 29, 30, 35).

Beside the positive impact of the different educational interventions, the best and most effective method to deliver such training to improve inhaler technique and clinical outcomes, remains unclear (25, 31).

The improved inhaler technique obtained after TTG education wanes within 30 days post-discharge. After the initial education provided upon inhaler prescription, only few patients later receive information or advice on how to use their devices and the inhaler technique deteriorates over time (13, 14).Thus, patient education needs to be reinforced; patients necessitate repeated instructions on inhalation technique to maintain long-term proper technique.

With increasing internet access among the population worldwide, technology-based interventions have been implemented and deemed effective alternatives to improve self-management of chronic conditions, including asthma (15-19). Previous studies showed that video-based intervention was more effective than written instruction or in-person TTG education in improving inhaler technique and main (18, 36).

Video-based instruction is thus considered an effective portable education intervention that remains accessible to patients for reinforcement of proper inhaler technique whenever needed.

